**10.3 Methods of Clinical Trial**

(1) Clinical Trial Design

The eligibility evaluation is conducted with the subject who underwent the modified radical mastectomy or breast preservation surgery and the axillary lymph node dissection at Asan medical center and signed at the consent form voluntarily subsequent to the screening test. The subject who isn’t included in the exclusion criteria visits the hospital on the operation day and undergoes the modified radical mastectomy or breast preservation surgery and the axillary lymph node dissection. Then, the subject is assigned to the investigational group or control according to the random assignment slip.

 EG: Guardix SG

 CG: Not applicable

That means the investigational device will be or won’t be applied onto the surgical site of subject depending on her group. Since the investigational device is applied inside of subject in the middle of surgery under anesthetic, the subject is unaware of treatment’s detail.

The related tests will be performed on the 7th, 3, 6 and 12 months subsequent to the surgery. In addition, the double-blind policy is maintained since the application of investigational device is performed by the expert who has a medical expertise and technique on the surgery and the application of investigational device, and the evaluator couldn’t know about the rule of random assignment and the allocation of subject to the group since the evaluator isn’t involved to the application of investigational device.

(2) Random Assignment of Subjects

In this clinical trial, random assignment was used to reduce bias that could be involved in the assignment of EG and CG, and to enhance the effects of comparison. To compare the precise difference in the range of motion of patient who underwent the partial mastectomy or total mastectomy, the subjects are assigned to each group randomly in similar proportion.

Our random assignment method is the block random assignment performed after generating random numbers (upto 4 places of decimals) for each subject using Excel’s random function (RAND). The sealed assignment slip is distributed to the subject. The sponsor of clinical trial provides the blinded slip which the investigational group or control is written down according to the randomly assigned subject table.

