**15-2 Safety Criteria Analysis**

(1) Adverse Events

All the AE that developed during the study period were analyzed. Their onset rate, the onset rate of AE that caused dropout, and the onset rate of SAE were summarized by group. They were coded using WHO-ART, then tested through the Chi-square test or Fisher’s exact test. The onset rates of AE were suggested as: onset rate of all adverse events, and the onset rate associated with the investigational device.

(2) Laboratory Tests

In the case of baseline continuous data from the laboratory test, descriptive statistics quantity (such as mean, SD, median, minimum, and maximum) was calculated, and their normal distribution was tested, then the difference between the groups was compared using One side, Two sample student t-test. In the case of categorical data, their descriptive statistics quantity (frequency and percentage) was suggested, and the difference between the groups was compared using the Chi-square test or Fisher’s exact test. After checking the investigational group’s test value came out on preoperative day and the 7th day following the surgery is different from it of control, we checked whether this difference is included within the normal error range or not.

1) Assessment of Criteria: Adverse events (Visit2, Visit3, Visit4, Visit5) and Hematologic Tests (Visit1, Visit2)

2) Evaluation criteria: The safety of investigational device is considered to be confirmed if the difference between the investigational group’s result value and control’s result value isn’t significant.

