**15-3 Statistical Analysis**

(1) Methods: One side, Two sample student t-test, Chi-square test, Fisher’s exact test

(2) Main analysis: ITT analysis

(3) Additional analysis: PP analysis

(4) Statistical power: 80%

* When performing the statistics for effectiveness evaluation, the information of subject who stopped to participate in or was dropped out from clinical trial is excluded from the compliance group (per protocol group) and is dealt as a missing value when the subject is assigned to the analysis group according to assignment table.

(5) General Principals of statistical analyses

The subject data of this study were analyzed through ITT (Intention to Treat) analysis and PP (Per Protocol) analysis.

In the ITT analysis, all the data obtained from the subjects who used the investigational device at least once after they were randomly assigned to the group were used. The above-mentioned subject’s information is excluded from the analysis for primary and secondary the missing value at the primary and secondary is discovered.

In the PP analysis, ITT analysis was data obtained from the subjects who completed the clinical trial according to the protocol were included. And the above-mentioned subject’s safety endpoint shall be included in ITT group. The value of subject which is out of clinical trial’s policy critically and may affect the efficacy evaluation (Exclusion criteria 2. The subject who is diagnosed as a breast cancer, absent on visit 1 and 2(each), assigned to the incorrect group, and experiences the severe adverse events during the clinical trial) will be included in the ITT group analysis with being excluded from the PP group analysis.

The efficacy evaluation was conducted using The efficacy evaluation was conducted using the ITT and PP analysis as a main method, while the PP analysis was used as an auxiliary method when the analysis results were inconsistent. The results of both analyses were compared. Demographical evaluation and safety evaluation were basically analyzed through the ITT analysis.

(6) Demographical Data

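### Safety is run in an ITT set whose definition does not fit a no-device control arm, and no safety set by treatment received is defined

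*Protocol*

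**What the plan says.** Four statements in the protocol bear on this.

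- **Safety set.** Section 15-3 (5): "Demographical evaluation and safety evaluation were basically analyzed through the ITT analysis".
- **Who is in the ITT set.** Same section: "all the data obtained from the subjects who used the investigational device at least once after they were randomly assigned to the group were used".
- **Wrong-group patients.** The same section lists several kinds of patient who leave the per-protocol set but stay in ITT, among them those "assigned to the incorrect group, and experiences the severe adverse events during the clinical trial) will be included in the ITT group analysis".
- **Safety verdict.** Section 15-2: "The safety of investigational device is considered to be confirmed if the difference between the investigational group’s result value and control’s result value isn’t significant". For adverse events the comparison is described as "They were coded using WHO-ART, then tested through the Chi-square test or Fisher’s exact test", with rates summarised by group.

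The control is no treatment at the wound. Section 10.3 says "the investigational device will be or won’t be applied onto the surgical site of subject depending on her group", and section 10.2 confirms that no comparator device is used. The protocol defines no safety set grouped by treatment received.

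**The concern.** Harm from a device left in the wound depends on whether it was applied, not on what the assignment slip said. A safety population therefore has to contain the unexposed controls and has to separate exposed from unexposed patients. The stated set does neither reliably. Its definition requires device use, which correctly treated controls do not have. If that is set aside and ITT is given its usual meaning, a control who received the device is tabulated with the patients who did not.

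The direction matters. In a superiority test of efficacy, such mixing works against the device. Under a rule that reads a non-significant difference as safe, the same mixing works in its favour.

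**Working it through.** **1. Side-by-side reading.** The ITT definition requires at least one use of the device. The control arm uses none. Taken literally, the between-group test in section 15-2 has no correctly treated control to compare with. A control given the device by mistake would be the only kind of control left in the set. The sentence therefore needs rewriting whatever the size of the dilution below.

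**2. Inputs for the ordinary-ITT reading.**
- Arm size n = 96, from section 8-3. That figure reproduces. For a margin of 10, a true difference of 15 and SD 10, the power at 86 per arm is 0.9032 (the table prints 0.90323), and 86/0.9 = 95.6, rounded up to 96. It serves here only as the arm size.
- Test: chi-square, from section 15-2. No level is stated for safety, so two-sided 0.05 is assumed.
- Event rates: not in the protocol. Assumed 5% without the device and 15% with it; a second scenario uses 10% and 20%.
- Number k of controls given the device: not in the protocol. Shown for 0 to 10.
- All patients assigned to the device are taken to have received it.

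**3. Formula.** As assigned, the control rate becomes ((n − k) × pC + k × pT)/n, so the expected difference shrinks by the factor (1 − k/n). For k = 5: (91 × 0.05 + 5 × 0.15)/96 = 5.30/96 = 5.52%, and the difference falls from 10.0 to 9.48 points. As received, the comparison is 96 − k unexposed with 96 + k exposed, at undiluted rates.

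**4. Results, 15% v 5%, power by exact enumeration.**

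| k | Control rate as assigned | Difference (points) | Power as assigned | Power as received |
|---|---|---|---|---|
| 0 | 5.00% | 10.00 | 0.663 | 0.663 |
| 1 | 5.10% | 9.90 | 0.651 | 0.651 |
| 2 | 5.21% | 9.79 | 0.639 | 0.659 |
| 3 | 5.31% | 9.69 | 0.627 | 0.640 |
| 5 | 5.52% | 9.48 | 0.602 | 0.646 |
| 10 | 6.04% | 8.96 | 0.542 | 0.644 |

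The as-received column is not smooth because the test is discrete. The chance of a 'safe' verdict is one minus power. As assigned it rises from 33.7% (k = 0) to 34.9% (k = 1), 39.8% (k = 5) and 45.8% (k = 10).

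**5. Second scenario, 20% v 10%.** The chance of a 'safe' verdict as assigned is 50.2%, 51.1%, 54.9% and 59.4% for k = 0, 1, 5 and 10. As received it stays between 50.2% and 51.1%.

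**6. Rare events.** Suppose three device reactions occur, one of them in a control given the device. As received the table reads 3 v 0; as assigned it reads 2 v 1. With 96 per arm, Fisher's exact test gives p = 0.25 and p = 1.0. The description changes, but the verdict under section 15-2 does not. (Moving one patient between columns alters the denominators trivially.)

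**The case against.** Several objections have force.

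- **A reader might infer that the protocol states safety is grouped as assigned.** It does not. The only wording that ties grouping to the assignment table, "is dealt as a missing value when the subject is assigned to the analysis group according to assignment table", comes in a note about effectiveness statistics. Sections 15-2 and 16-1 say only that events are summarised by group. As-assigned grouping is an inference from the usual meaning of ITT and from keeping wrong-group patients in the set.
- **A reader might infer that the protocol expects controls to receive the device.** It does not say so. The wrong-group item is one entry in a list of per-protocol exclusions and may mean an allocation error. Application is a single act in theatre at one centre, and nothing supports five or ten misapplied controls.
- **There is a partial safeguard.** Section 15-2 also asks for the rate of device-associated events, and the causality assessment in section 16-4-1 begins with actual exposure. A device reaction in a mis-treated control could be flagged as device-related. The protocol does not say in which arm's column it would appear.
- **Analysis-set detail often belongs in the SAP.** That is true of detail left open. Here the protocol fixes the set, and a SAP that followed it would inherit the problem.
- **The verdict rule is the larger fault.** This stands. With no misapplication at all, a true rise from 10% to 20% is called safe about half the time (50.2%). That aggravates the present point and does not remove it.

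**Conclusion.** The point holds in a limited form. The stated safety population cannot serve as written, because its definition excludes correctly treated controls, and nothing says how a patient whose assigned and received treatments differ is counted for safety. On the ordinary reading of ITT, the bias runs towards a finding of safety.

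Its size is modest. One misapplied control lowers power by about one percentage point, and in the 15% v 5% scenario regrouping recovers none of it. Five would lower power from 0.663 to 0.602, against 0.646 by treatment received. These figures rest on assumed event rates, an assumed two-sided 5% level and assumed misapplication counts. It would go too far to say that dilution will drive the trial's safety conclusion. The documents give no basis for expecting many such patients, and in the rare-event example the verdict is the same under either grouping. The change is still worth making because it corrects a stated rule at almost no cost.

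**What to change.** In section 15-3 (5), replace the sentence that places safety in the ITT set. Define a safety set of all randomised patients who were operated on, including controls who received no device, grouped by whether the device was actually applied. Use it for the analyses in sections 15-2 and 16-1, and keep as-assigned safety tables as supportive. Efficacy stays grouped as assigned.

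The cost is one sentence and a record of device application for each patient. The clinical trial schedule already lists the device at Visit 2; the CRF is not shown, so whether it records application in both arms should be checked. No extra patients or visits are needed. This change does not repair the rule that a non-significant difference confirms safety, which needs its own correction.

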**16. Assessment of Safety Criteria, and Evaluation and Side Effect Report (including adverse events)**

**16-1 Assessment of Safety Methods**

The adverse events confirmed at the physico-chemical exam or reported from the subject are included in the analysis for evaluating the occurrence rate of adverse events which occurred within the investigational group and control and its severity and its type.

(1) Adverse events

All the AE that developed during the study period were analyzed. Their onset rate, the onset rate of AE that caused dropout, and the onset rate of SAE were summarized by group. They were coded using WHO-ART, then tested through the Chi-square test or Fisher’s exact test. The onset rates of AE were suggested as: onset rate of all adverse events, and the onset rate associated with the investigational device.

(2) Laboratory Tests

In the case of baseline continuous data from the laboratory test, descriptive statistics quantity (such as mean, SD, median, minimum, and maximum) was calculated, and their normal distribution was tested, then the difference between the groups was compared using the independent t-test or Wilcoxon’s rank sum test. In the case of categorical data, their descriptive statistics quantity (frequency and percentage) was suggested, and the difference between the groups was compared using the Chi-square test or Fisher’s exact test.

**16-2 Adverse Events Definitions**

(1) Adverse Events, AE

AE is all the unintended syndromes (including signs and lab test results), symptoms, or diseases, which develop in the subjects during the clinical trial period. They are not necessarily associated with the investigational device. Expected daily fluctuations in the test disease or previous clinical manifestations, which are not clinically significant, are not required to be reported.

All AE that developed since the beginning of the clinical trial must be reported. The time of starting the clinical trial is the time of receiving the signed written consent. (Written consent must be obtained before special diagnoses or treatment is started.) All the AEs that developed after the written consent was received must be reported regardless of the administration or association with the investigational device.

(2) Adverse Device Effects, ADE

ADE is the hazardous and unintended reactions caused by the investigational device, whose causal relationship with the investigational device cannot be denied.

(3) Serious AEs · ADEs

One of the following AE or ADE that developed during the clinical trial period due to the investigational device.

1) Death or life-threatening danger

2) Hospitalization or extension of hospitalization

3) Permanent or serious impairment, or deteriorated functions

4) Fetal deformity or anomaly

(4) Unexpected Adverse Device Effects, UADEs

Not considered as significant ADE patterns and hazards according to the information related to the investigational device, as specified in the Investigator’s brochure or attached documents.

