**16-6 SAE**

(1) Definition of SAE

SAE means cases of death, life-threatening events, hospitalization or extension of hospitalization, continuous or critical disability/incapacitating, or congenital deformity or impairment of the offspring of subjects. Death, non-life-threatening events, and cases not requiring hospitalization can be regarded as SAE when they harm the patients or subjects, or when medical or surgical measures are required to prevent the results listed in the definition section above.

1) Definition of "Life-Threatening"

If the development of AE has the possibility resulting in an immediate death of the subject, the AE is life-threatening. However, an AE, which can induce death if the AE becomes more serious, is not included in this category.

2) Definition of "Disability/Incapacitating"

If a patient has an AE that causes substantial or continuous difficulties hindering normal life, the patient is suffering from AE with temporary or continuous disabilities.

3) Definition of "Hospitalization"

AE requiring hospitalization thought to be serious. Preplanned surgery or hospitalization, which was arranged for baseline symptoms with mild severity or frequency prior to the clinical trial, is not classified as AE.

If undesirable symptoms develop during the planned process, those must be reported as serious or non-serious AE according to the classification criteria. These usually involve staying in a ward or emergency room for at least one night because the subject could not be properly treated in the clinical doctor’s office or outpatient clinic. Cases on the border line of hospitalization are regarded as SAE.

4) Definition of "Routine Clinical Procedure"

A clinical procedure that can develop during the clinical trial period but not inhibiting the normal procedure of the protocol

5) Others

Cases of life-threatening, death, or critical risks not requiring hospitalization, which require internal or surgical intervention for preventing the above-mentioned developments, must be addressed with medical or scientific measures. These cases are also regarded as SAE.

(2) SAE Report

1) The investigator must promptly report all the serious and unexpected AE cases (including ADE, serious AE/ADE) to investigators, IRB and MFDS within the period as stated below.

(A) Death or life-threatening cases: Within 7 days after the sponsor was notified of or acknowledged the case. Details must be additionally reported within 8 days of the initial report date.

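### The protocol defines a serious adverse event in two incompatible ways, with and without device causation, and does not say which one governs the by-group SAE rate

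*Protocol*

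**What the plan says.** Section 16-2 (3) of the protocol, headed for serious AEs and serious ADEs together, defines them as "One of the following AE or ADE that developed during the clinical trial period due to the investigational device" and then lists the qualifying outcomes.

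Section 16-6 (1), the definition of SAE, sets no causal condition: "SAE means cases of death, life-threatening events, hospitalization or extension of hospitalization, continuous or critical disability/incapacitating", followed by congenital harm to offspring and by events that need intervention to prevent such outcomes.

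Section 16-2 (1) defines adverse events broadly. It says "They are not necessarily associated with the investigational device" and that all events after consent "must be reported regardless of the administration or association with the investigational device".

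For the analysis, section 15-2 (1) says "the onset rate of SAE were summarized by group", and section 16-1 repeats this. On testing, 15-2 says "They were coded using WHO-ART, then tested through the Chi-square test or Fisher’s exact test". Both sections separate the rate of all adverse events from the rate of device-associated events. Neither makes that split for SAEs or points to a definition of SAE.

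Sections 10.2 and 10.3 state that nothing is applied in the control group.

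**The concern.** A between-group SAE comparison needs one definition that can be met in the same way in both groups. The wording of 16-2 (3) cannot be, because a subject who never received the device cannot have an event caused by it.

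Three things are at stake if a site or analyst works from 16-2 (3):

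- The control group's SAE count is fixed at zero in advance.
- The device group's count depends on individual causality judgements as well as on what happened to the patients.
- A death or readmission judged unrelated to the device could be treated as not an SAE, and so miss the 24-hour report to the sponsor in 16-3.

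Section 15-2 also treats a non-significant group difference as confirmation of safety, and it names adverse events among the criteria assessed. The definition therefore feeds a stated conclusion as well as a table.

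**Working it through.** **1. The two definitions side by side**

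| | 16-2 (3) | 16-6 (1) |
|---|---|---|
| Outcome condition | Listed serious outcomes | Similar list, plus events needing preventive intervention |
| Causal condition | Due to the device | None |
| Can a control subject qualify? | No | Yes |
| Can an unrelated event in the device group qualify? | No | Yes |

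The sentence in 16-2 (3) covers AEs as well as ADEs, so as written the causal limit is not confined to serious ADEs. The causality checklist in 16-4-1 asks first whether the subject was exposed to the device; for a control the true answer is no. A blinded assessor might still label a control event as device-related, but that would be a misattribution and would not make the definition workable.

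**2. Inputs for an illustration of size**

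- Group size: 86 evaluable per group and 10% drop-out (section 8-3). 86 / (1 − 0.10) = 95.6, rounded up to 96, which matches the protocol.
- SAE rate: not given. Assumed range 2% to 10% per group, the same in both groups.
- Share of device-group SAEs attributed to the device: not given. Left to vary.

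**3. Fisher's exact test with the control count fixed at 0**

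With equal groups of 96 and x events, all in the device group, the two-sided p-value is 2 × C(96, x) / C(192, x). For x = 2 this is 2 × (96 × 95) / (192 × 191) = 18,240 / 36,672 = 0.497.

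| Device v control | Two-sided p |
|---|---|
| 2 v 0 | 0.497 |
| 5 v 0 | 0.059 |
| 6 v 0 | 0.029 |
| 8 v 0 | 0.007 |

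The 0.05 threshold is crossed at the sixth attributed event. With 86 per group it is crossed at the same point (5 v 0: 0.059; 6 v 0: 0.029).

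An assumed case shows the spread. Suppose 8 subjects in each group have a serious event. Under 16-6 the table is 8 v 8 and p = 1. Under 16-2 (3) it is 2 v 0 (p = 0.50) if two device-group events are attributed, and 8 v 0 (p = 0.007) if all eight are.

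**4. Chance of a significant difference when the true all-cause rates are equal**

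Under 16-2 (3) the device-group rate that counts is q = (all-cause rate) × (share attributed), taking attributions as independent. The test rejects when X ≥ 6, with X binomial (96, q). Under 16-6 both groups are drawn from the same all-cause rate.

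| Rate | 16-6, both groups at this all-cause rate | 16-2 (3), q equal to this rate, control 0 |
|---|---|---|
| 2% | 0.4% | 1.3% |
| 5% | 2.0% | 34.8% |
| 10% | 2.8% | 92.7% |

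Reading the last column at the same rate as the middle one assumes that every device-group SAE is attributed to the device, which is the worst case. An all-cause rate of 10% with half attributed gives q = 5%, hence 34.8%. With one fifth attributed, q = 2%, hence 1.3%.

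**The case against.** The strongest reply is that 16-6 plainly governs. It is the section titled SAE, it contains the subsection defining SAE, and it elaborates life-threatening, disability and hospitalization. The analysis sections use the term SAE. By contrast, 16-2 (3) is a short glossary entry that is hard to apply literally: under 16-2 (2) an event the device may have caused is already an ADE, so a causal limit leaves the reference to AEs almost empty. On this reading the planned comparison is sound. Much of this stands. It makes 16-6 the likelier intention, but no sentence in the protocol says so, and 16-2 is the definitions section that an investigator would consult.

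A reader might go further and infer that the SAE comparison is meaningless and that serious events go uncounted. The documents do not support that. The structural zero arises only if 16-2 (3) is the rule used. Sections 16-2 (1) and 16-3 require adverse events to be recorded whatever their relation to the device, with outcome and causality noted as separate items, and 15-2 and 16-1 analyse all adverse events. What could be lost is the serious label and the urgent report, while the event itself stays on record. Section 16-7 also asks the principal investigator to report all SAEs at once, which protects reporting, provided that SAE is read as in 16-6.

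It is also fair to say that the figures rest on assumed rates, and that 8 v 8 and 2 v 0 are both non-significant and so lead to the same conclusion under 15-2. The illustration shows how far the result could depend on attribution. It does not predict what the trial will find.

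**Conclusion.** The contradiction is real and should be corrected. The protocol states two definitions of a serious event that differ on causation, and it plans a by-group SAE rate without choosing between them.

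The consequence is conditional. Under 16-6 the comparison is interpretable. Under 16-2 (3) the control count is zero by definition and the device-group result follows causality judgements. With equal true rates, the chance of a significant difference then runs from 1.3% to 92.7% for attributed rates of 2% to 10%, against 0.4% to 2.8% under the all-cause definition at the same rates. Those percentages assume 96 per group, a two-sided Fisher's test at 0.05, and SAE and attribution rates that the protocol does not give.

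This is a defect of definition. The range-of-motion endpoint, the sample size, the power and the significance level are untouched. The wording may come from translation, but sites apply the text as it stands, and an analysis plan written later cannot restore an urgent report that was not made.

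**What to change.** - In 16-2 (3), remove the causal condition so that seriousness is defined by outcome in both groups. A cross-reference to 16-6 (1) is the simplest way, since its outcome list is the fuller one.
- Define a serious ADE as a separate category: an SAE that also meets the causal wording of 16-2 (2). Cite 16-2 (2) and not 16-8 (1), because the latter repeats the text that 16-2 (4) uses for unexpected effects.
- In 15-2 and 16-1, state that the by-group SAE rate is all-cause, and list serious ADEs separately if wanted.

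The cost is a wording amendment to three sections and possibly somewhat more SAE forms. If events have already been classified under 16-2 (3), the recorded adverse events in both groups would need one review against 16-6 (1). No analysis method or sample-size figure changes.
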